## Abstract

****Background**:**

Despite evidence-based recommendations supporting long-term use of cardiac medications in patients post ST-elevation myocardial infarction, adherence is known to decline over time. Discontinuation of cardiac medications in such patients is associated with increased mortality.

****Methods/design**:**

This is a pragmatic, cluster-randomized controlled trial with blinded outcome assessment and embedded qualitative process evaluation. Patients from one health region in Ontario, Canada who undergo a coronary angiogram during their admission for ST-elevation myocardial infarction and who survive their initial hospitalization will be included. Allocation of eligible patients to intervention or usual care will take place within one week after the angiogram using a computer-generated random sequence. To avoid treatment contamination, patients treated by the same family physician will be allocated to the same study arm. The intervention consists of recurrent, personalized, paper-based educational messages and reminders sent via post on behalf of the interventional cardiologist to the patient, family physician, and pharmacist urging long-term adherence to secondary prevention medications. The primary outcome is the proportion of patients who report in a phone interview taking all relevant classes of cardiac medications at twelve months. Secondary outcomes to be measured at three and twelve months include proportions of patients who report: actively taking each cardiac medication class of interest (item-by-item); stopping medications due to side effects; taking one or two or three medication classes concurrently; a perfect Morisky Medication Adherence Score for cardiac medication compliance; and having a discussion with their family physician about long-term adherence to cardiac medications. Self-reported measures of adherence will be validated using administrative data for prescriptions filled.

****Discussion**:**

This intervention is designed to be easily generalizable. If effective, it could be implemented broadly. If it does not change medication utilization, the process evaluation will offer insights regarding how such an intervention could be optimized in future.

****Trial registration**:**

Clinicaltrials.gov NCT01325116

## Background

### **Cardiovascular disease burden and the role for long-term pharmacotherapy**

Worldwide, cardiovascular disease (CVD) is estimated to be the leading cause of death and disability [1]. Approximately 50% of myocardial infarctions (MIs) and 70% of CVD deaths occur in patients who have already documented coronary artery disease (CAD) [2]. Therefore, the prompt identification of modifiable cardiovascular risk factors and initiation of proven secondary preventative medications post-MI are essential to the prevention of subsequent cardiac events [3]. Population-level observational studies provide evidence that the rate of cardiovascular morbidity and mortality has been decreased through the use evidence-based therapies [4,5].

ST-segment elevation myocardial infarction (STEMI) is a common presentation of acute myocardial infarction (AMI) constituting approximately 30% of all cases [6]. Post-STEMI, patients are at high risk for subsequent cardiac events—18% of men and 35% of women will have a repeat MI within six years and STEMI patients have four to six times the risk of sudden cardiac death compared to the general population [7]. While acute treatment is crucial for STEMI patients, relevant guidelines emphasize that the initiation and long-term maintenance of evidence-based secondary preventative therapies are essential for reducing the overall burden of CVD [3,8,9].

### **Poor long-term adherence to cardiac medications**

While there is a significant body of evidence supporting these guidelines (Table 1), there remains a large gap between ideal and actual care with regard to the long-term management of cardiovascular risk for these patients. Studies show that adherence to evidence-based therapies begins decreasing at 30 days and falls to as low as 50% adherence at six months post-discharge [10-14]. Unfortunately, discontinuation of evidence-based therapies has repeatedly been shown to be associated with increased mortality in patients with CAD [15-18].

**Table 1 T1:** Summary of guideline recommendations for medications post-STEMI

**Medication**	**Recommendation**		**Strength of evidence***
Anti-platelets	Aspirin therapy (75-162 mg/day) indefinitely post-STEMI.		I A
	P2Y_12_-receptor inhibitor (clopidogrel, prasugrel, or ticagrelor) in combination with aspirin in patients post ACS		I A
	P2Y_12_-receptor inhibitor continued for at least 12 months if ACS managed with PCI and stent placement		I A
Statins	Statin therapy indefinitely for all patients with a prior cardiovascular event.		I A
Angiotensin-system agent	ACE inhibitor (or ARB if intolerant) post-STEMI indefinitely for all patients with left ventricular ejection fraction <40% and in those with hypertension, diabetes, or chronic kidney disease		I A
	ACE inhibitor (or ARB) for all patients post-STEMI		IIa B
Beta-blockers	Beta-blockers for all patients post-STEMI		I A
	Beta-blockers continued for at least three years post-STEMI		I B

*Strength of Evidence.

I: Conditions for which there is evidence and/or general agreement that a given treatment is beneficial, useful, and effective.

IIa: Weight of evidence/opinion is in favor of usefulness/efficacy.

A: Data derived from multiple randomized clinical trials or meta-analyses.

B: Data derived from a single randomized trial, or nonrandomized studies.

Medication non-adherence is increasingly recognized as a very important issue due to its significant health consequences [19,20]. Many reasons for non-adherence have been proposed and these can generally be categorized as provider-level (*e.g.*, knowledge, motivation, time), patient-level (*e.g.*, knowledge, motivation, finances [21]), and system-level (*e.g.*, access to care, coordination of care). Furthermore, both ethnicity [22,23] and socio-economic status [24] seem to be related to quality of care for cardiovascular disease, even in countries with universal healthcare like Canada and the United Kingdom (UK), and non-adherence related to such factors may not be readily impacted with quality improvement interventions.

Fortunately, the evidence suggests that many of the key factors contributing to cardiac medication non-adherence may be amenable to intervention. Discontinuation of evidence-based cardiac medicines post-STEMI is rarely due to an active, informed choice after discussion of risks and benefits between patient and health-care-provider; absolute contraindications are rare and side effects are infrequently reported by patients as the primary reason for discontinuation (less than 4% of patients) [25,26]. In contrast to situations where informed decisions are made to deviate from standard treatment protocols, qualitative work in primary care has found that poor adherence may be frequently due to fragmented systems of care [27] or communication problems at the interface between secondary and primary care [28]. A recent study in Canada has highlighted the risk related to transitions in care; it appears that hospitalizations increase the risk for inadvertent discontinuation of cardiac medications [29].

The provider also can have an impact; having a cardiologist involved in the patient’s care may increase rates of appropriate medication adherence [30]. However, there is undesirable variation among prescription rates by specialists as well. In one study of cardiologists, the most common reason given for not prescribing secondary prevention medications was, ‘not high-enough risk’ [25]. However, in that study, risk scores of patients not treated for this reason were often higher than those of patients prescribed such treatment. Meanwhile, the same study found that approximately one-third of patients had stopped their medication without instruction from their doctor. This indicates a potential role for multi-pronged interventions addressing both the provider and the patient.

### **Previous research aiming to improve adherence**

Numerous systematic reviews have been published regarding interventions to improve adherence to medications. An overview of reviews found that no patient-mediated interventions were effective across all diseases, but found that the most promising interventions included self-management, simplified dosing, and involvement of pharmacists [31]. A review focusing on anti-depressants found that patient education alone was ineffective [32], and a review focusing on anti-epileptics found that patient education was inconsistent, while interventions with multiple reminders featuring action planning were more often effective [33]. Recognizing that non-adherence tends to worsen over time, a recent Cochrane review recommended testing a delayed intervention as opposed to the immediate reminders used in similar previous trials [34], as one would expect a larger effect size in a delayed intervention.

One previous trial has shown that brief evidence summaries regarding medications attached to discharge letters sent to primary care providers resulted in improved adherence [35]. Three other trials have evaluated the role of reminder letters to the primary care provider (with or without patient reminders) to improve adherence to evidenced-based cardiovascular therapies: one in the USA, one in the UK, and one in Canada [36-38]. The American trial focused on beta-blocker use post-MI and found a small increase in compliance (proportion of days covered), with a number needed to treat of 16 for achieving high adherence, but no change in the proportion who discontinued their beta-blocker. The other two trials focused on statin use in patients with known CAD. These trials found absolute increases in adherence of 9% to 10% in statin use, but despite this being a potentially important effect size on a population basis, both were under-powered for effects this size.

## Objectives

The overarching goal of this project is to improve long-term use of secondary prevention medications for patients with CAD, and thereby reduce cardiovascular events through the use of an easily generalizable and sustainable intervention. The primary objective of this study is to assess if repeated mailing of an educational message and reminder to the family physician and the patient will decrease the proportion of patients who discontinue evidence-based secondary-prevention medications at twelve months post-STEMI. A secondary objective is to encourage cardiac patients and their primary care providers to discuss the benefits of long-term adherence to cardiac medications.

## Methods/design

### **Study design**

DERLA-STEMI is a pragmatic, cluster-randomised controlled trial, with blinded outcome-assessment, and is registered with clinicaltrials.gov (NCT01325116). See Study Flow Diagram (Figure 1).

**Figure 1 F1:**
[figure not shown]
Study Flow Diagram.

### **Participants and Setting**

In Ontario, healthcare is financed through a single-payer (publicly administered) system. There are no co-payments for visits to generalist or specialist physicians or for care provided in hospitals for patients of any age, and almost all licensed prescription medications are covered for patients 65 and over. Patients younger than 65 years pay for medications out-of-pocket or through private insurance plans, or are covered by the provincial plan if they qualify for social support.

In this study, eligible patients are adult patients (>18 years) with a diagnosis of STEMI, who undergo a coronary angiography procedure (with or without angioplasty), at the Heart Investigation Unit (HIU) in Hamilton, Ontario, and who are alive at hospital discharge. In keeping with the pragmatic approach to study design, no other exclusion criteria will be applied. The HIU is the only catheterization lab in its region, with a catchment population of almost 1.5 million people. More than 700 STEMI patients undergo an angiogram there each year. Studies at the HIU have highlighted excellent rates of prescribing of evidence-based therapies at discharge post-STEMI, but substantial reduction in use starting three months following discharge [39,40]. While 78% of STEMI patients leave the HIU taking a statin, an ACE-inhibitor (or ARB), a beta-blocker, and aspirin, by 90 days the proportion still taking all four of these medication classes falls to 63% (unpublished data from the Strategic Management of Acute Reperfusion and Therapies in Acute Myocadial Infarction (SMART-AMI) study).

### **Intervention**

The intervention was developed in concert with clinical experts from both primary care and cardiology, as well as experts in knowledge translation and medical decision-making. Personalized letters sent via post to the patient and their family physician at one, five, eight, and eleven months after their angiogram, signed by the interventional cardiologist (see Additional file 1: Appendix A for prototype). The letter for the family physician names the patient and provides brief evidence in support of long-term medication use for these patients. This was reviewed and edited with a series of family physicians from a different area of the province.

The patient letter provides a review of the importance and role of each of the cardiac medications and urges short- and long-term adherence (see Additional file 1: Appendix B for prototype). This educational aspect is designed to address knowledge and beliefs about medication use as a potential cause of poor adherence. The intervention explicitly encourages discussion of medication adherence with the family physician by asking patients to bring the letter to their family physician. It also asks patients to deliver the final page of their letter to their pharmacist; this page is written to the pharmacist urging them to participate in promoting long-term adherence. The intention is to facilitate recurrent discussions with primary care providers that emphasize long-term adherence and to address coordination of care and continuity of information as barriers to medication persistence. This letter was developed with iterative evaluations of understanding and acceptability amongst a series of cardiology patients at the HIU. The language in the patient letter is simplified to a grade six-level.

The timing of the intervention was specifically chosen based on the preliminary data obtained from the SMART-AMI trial demonstrating suboptimal rates at 90 days. Furthermore, literature (referenced above) demonstrates that adherence starts decreasing by thirty days and continues to decrease in an almost linear fashion. Finally, the common practice in Ontario is for pharmacists to dispense medications for no more than three months at a time (regardless of duration of the prescription ordered by the physician). Therefore, we decided to deliver the intervention at regular intervals (1, 5, 8, and 11 months post-STEMI) corresponding to the likely time periods prior to patients requiring a prescription renewal/refill. In pilot testing the intervention with family physicians and patients, we determined that sending the full letter too frequently would be undesirable and that the physicians in particular did not want to have monthly reminders. At the same time, close examination of data from Ontario indicated large stepwise declines in adherence at 30 and 60 days post-STEMI. To address this, patients will be provided an additional postcard type reminder two months post-STEMI (see Additional file 1: Appendix C).

In summary, the unique aspects of the intervention compared to usual care include the following: the letter to the primary care provider is personalized and includes a summary of the evidence in support of long-term adherence and represents a recurrent form of contact between the cardiologist and the primary care provider; the letter to the patient use clear language suitable for a broad range of health literacy levels and was iteratively refined with input from patients in the target population, features content that attempts to address adherence-related beliefs, and provides explicit, actionable instructions to discuss the matter with the family physician as well as a summary to be given to the outpatient pharmacist to facilitate coordination of renewals.

### **Comparator/usual care**

Usual care in this context may include some contact between the admitting physician (generally not the interventional cardiologist) for the STEMI patient and the primary care provider (generally the family physician). This is usually in the form of a standard discharge summary mailed to the family physician’s office at the end of the hospitalization. The quality of such discharge summaries varies widely even within the same institution (and summaries frequently lack necessary information regarding medications) [41]. In keeping with the pragmatic nature of the trial, no attempt will be made to standardize the usual care arm [42].

### **Allocation**

The randomization schedule was computer-generated by a statistician independent of the study, using a permuted block design with randomly varying block lengths of four, six, or eight. Eligible patients are randomly allocated to one of the two treatment arms. Although enrolment of more than one patient treated by a particular family physician is expected to occur infrequently, randomization will be carried out to ensure that, once a patient from any family physician is randomized, all future patients seen by that family physician will automatically be assigned to the same arm. This is necessary to avoid contamination (with one family physician having patients in different intervention arms). Roughly one-half of patients will be allocated to each study arm (the actual allocation ratio will depend on the size of the clusters). Based on pilot data, we anticipate that approximately 10% to 15% of patients will not have a family physician. In keeping with the pragmatic design of the trial, a patient without a family physician will be included (receiving only the patient-level intervention).

Randomization is delayed by one week (after the angiogram) to permit time to identify and exclude patients with in-hospital death. Randomization will continue until the target sample size is achieved. The anticipated duration of enrolment is 15 months. The allocation sequence will be concealed from the investigators and outcome assessors; only the study coordinator who will be sending out the letters will have access to the un-blinded allocation list.

### **Outcomes**

The primary outcome is the proportion of living patients who describe taking all cardiac medication classes of interest measured at twelve months. This type of ‘all-or-none’ measure has been recommended for evaluating quality improvement interventions, especially related to medication utilization [43]. Specifically, we will assess whether patients are taking a statin, beta-blocker, angiotensin modifier (ACE or ARB), and aspirin at twelve months. All STEMI patients have reasonable evidence supporting these medications [3]; we anticipate that randomization will balance those patients for whom evidence is less clear or who might have contraindications to any of these medications.

We will also assess whether patients are taking these four medication classes plus a secondary antiplatelet (clopidogrel, prasugrel, or ticagrelor) at three months. Therefore, patients at three months will be dichotomized as to whether or not they are taking all five cardiac medication classes, and at twelve months they will be dichotomized according to whether they are taking all four relevant medication classes. The difference in the number of medication classes considered at three and twelve months relates to uncertainty in the evidence regarding the appropriateness of a secondary antiplatelet at this timeframe. Additional secondary outcomes include a comparison of: the proportion of patients who report actively taking each cardiac medication class of interest (item-by-item) at three and twelve months; the proportion of patients who report stopping medications due to side effects at three and twelve months; the proportion taking one or two or three medication classes concurrently at three and twelve months; and the proportion of patients with a perfect Morisky Medication Adherence Score (MMAS) for cardiac medication compliance at three and twelve months. The MMAS is a brief, standardized adherence questionnaire which excellent reliability [44], and has been shown to be predictive of cardiovascular medication adherence [45] and to be associated with control of blood pressure and cholesterol [44,46]. In addition, all patients will be asked at three months and twelve months whether they had a discussion with their family physician during past three months in which the provider had encouraged long-term cardiac medication compliance.

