### **Data collection**

Baseline patient characteristics will be obtained from standard patient-registry information at the HIU. This includes demographic information, comorbidities, and the findings at the time of angiography.

Outcomes will be assessed 3 and 12 months post-index angiogram through patient phone calls by a research coordinator associated with the HIU who will be trained expressly for this function. The research coordinator conducting the phone calls will not have access to the allocation list. The calls are made on behalf of the treating cardiologist at the HIU, and all patients will be encouraged to review cardio-protective meds with their family physician. The phone call follow-ups will ask patients to list their current, daily medications (and doses) without specific prompting in order to reduce bias. Attempts will be made to contact patients for a maximum of 30 days prior to being considered lost-to-follow-up. Reasons for loss-to-follow-up will be tracked.

For a sample of patients aged 65 and older, the Ontario Drug Benefit database will be used to examine the accuracy of the self-reported primary outcome and to further evaluate adherence using the medication possession ratio over the preceding year, which has been shown to be associated with both pill counts and clinical effects [47].

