### **Sample size**

The sample size for this design is based on the following assumptions: an assumed absolute increase in the proportion of patients taking all four cardiovascular medication classes of 11% at twelve months post-STEMI; an estimated control group proportion of 50%, and a variance inflation factor of 1.02 (derived from an intra-cluster correlation coefficient of 0.019 calculated from data in the SMART-AMI registry and assuming an average cluster size of 1.2 based on pilot data). To achieve 80% power to detect a significant main effect of the intervention using a Chi-squared test at the 5% level of significance, 652 patients would be required. We will randomize 815 patients to account for an estimated participation rate of 80% at the 12-month follow-up. This dropout rate is conservative based on similar studies at the HIU where the participation rate has been greater than 90% over even longer time periods [40].

The expected effect size is slightly higher than the effect seen in the previous Canadian trial to account for the fact that the intervention is multifaceted (directed at both physician and patient) and occurring later post-STEMI (reducing the expected control group rate and therefore the possibility of a ceiling effect). Based on this sample size calculation, and the rate of STEMI patients presenting to the HIU, we anticipate that it will take approximately 15 months to complete the recruitment for this study.

We will use a kappa statistic to assess agreement between the self-report of the primary outcome and the corresponding objective data from the Ontario Drug Benefit database. Based on an anticipated overall proportion of 56% at 12 months (average of intervention and control arm) and an anticipated kappa of 0.88, we would consider acceptable agreement if the lower limit of the 95% confidence interval around kappa does not drop below 0.80. Therefore we will evaluate validity of the primary outcome in a random selection of 138 patients aged 65 or greater.

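### Validating a composite that includes aspirin against prescription claims can make accurate self-report look like over-reporting

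*Protocol article*

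**What the plan says.** Outcomes defines the primary outcome as taking every class of interest at twelve months: "we will assess whether patients are taking a statin, beta-blocker, angiotensin modifier (ACE or ARB), and aspirin at twelve months". Under Data collection, the telephone interviewer will "ask patients to list their current, daily medications (and doses) without specific prompting", so aspirin counts however the patient came by it.

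The same section plans a check in a subset of those who are at least 65: "the Ontario Drug Benefit database will be used to examine the accuracy of the self-reported primary outcome". The abstract describes the reference data: "Self-reported measures of adherence will be validated using administrative data for prescriptions filled". Participants and Setting describes drug coverage at this age only for prescription drugs: "almost all licensed prescription medications are covered for patients 65 and over".

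Sample size fixes the comparison as "agreement between the self-report of the primary outcome and the corresponding objective data from the Ontario Drug Benefit database", using a kappa statistic. It gives an "anticipated overall proportion of 56% at 12 months", an anticipated kappa of 0.88, and a random selection of 138 patients. Agreement is acceptable if the lower 95% confidence limit of kappa does not fall below 0.80.

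No section takes aspirin out of the validated composite, names a second source for it, or lists the matter among the limitations of self-report.

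**The concern.** The two sides of the kappa table do not measure the same thing. Self-report records use of aspirin; the reference records prescriptions filled. Aspirin can be obtained without a prescription, and then it may leave no claim.

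The effect is confined to one kind of patient: someone who reports all four classes and has claims for the statin, the beta-blocker and the ACE inhibitor or ARB. If the aspirin left no claim, the all-or-none rule turns the claims result from yes to no, and an accurate report becomes a disagreement. If claims for another class are missing as well, the claims composite is already negative and aspirin changes nothing.

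The error runs one way, self-report yes and claims no. That is the pattern over-reporting would produce, and over-reporting is the main thing such a validation should detect. The article acknowledges its reliance on self-report as a caveat and offers this comparison in response. A low kappa on the composite could not be read as evidence about the accuracy of self-report without knowing how the aspirin was obtained.

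**Working it through.** **Inputs from the Sample size section:** proportion p = 0.56, anticipated kappa k = 0.88, lower-limit criterion 0.80, n = 138. **Assumed:** f, the share of patients otherwise positive for all four classes in claims whose aspirin leaves no claim. The document gives no value, so a range is shown.

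**Step 1: reproduce 138.** For two binary ratings with common prevalence p, the large-sample variance of kappa is V/n, with

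V = (1−k)[(1−k)(1−2k) + k(2−k)/(2p(1−p))].

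Here 2p(1−p) = 2 × 0.56 × 0.44 = 0.4928 and k(2−k) = 0.88 × 1.12 = 0.9856, so

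V = 0.12 × [0.12 × (−0.76) + 0.9856/0.4928] = 0.12 × 1.9088 = 0.2291.

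n = 1.96² × 0.2291 / (0.88 − 0.80)² = 137.5, rounded up to 138. The plan's figure is reproduced. The planned sample therefore puts the expected lower limit almost exactly at 0.80, with no slack.

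**Step 2: self-report and claims otherwise in perfect agreement.** The cells (self-report, claims) are: yes/yes 0.56(1−f), yes/no 0.56f, no/yes 0, no/no 0.44. Observed agreement is 1 − 0.56f and chance agreement is 0.5072 − 0.0672f, so

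kappa = 0.4928(1−f) / (0.4928 + 0.0672f).

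At f = 10% this is 0.44352/0.49952 = 0.888. At f = 20% it is 0.39424/0.50624 = 0.779. Setting kappa = 0.80 gives f = 0.09856/0.54656 = 18.0%.

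**Step 3: start from the planned kappa of 0.88.** The off-diagonal cells are each 0.12 × 0.56 × 0.44 = 0.0296, so yes/yes is 0.5304 and no/no is 0.4104. A share f of everyone positive in claims is then moved to claims-negative. At f = 10%, observed agreement is 0.8908 and chance agreement 0.5005, so kappa = 0.3903/0.4995 = 0.781.

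**Step 4: lower 95% limits at n = 138.** These use the Fleiss–Cohen–Everitt standard error, which allows unequal margins.

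| f | Otherwise perfect: kappa (lower limit) | From 0.88: kappa (lower limit) |
|---|---|---|
| 0% | 1.000 (1.000) | 0.880 (0.800) |
| 2% | 0.977 (0.942) | 0.860 (0.774) |
| 5% | 0.944 (0.888) | 0.830 (0.737) |
| 10% | 0.888 (0.812) | 0.781 (0.678) |
| 15% | 0.833 (0.742) | 0.733 (0.621) |
| 20% | 0.779 (0.677) | 0.685 (0.568) |
| 30% | 0.672 (0.558) | 0.592 (0.467) |

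**Step 5: where the criterion fails.** With otherwise perfect agreement, the lower limit passes below 0.80 at f = 10.85%, which is 0.1085 × 0.56 × 138 = 8.4 patients, so 8 or 9 of the 138. Kappa itself passes below 0.80 at about 18%, or 14 patients. Starting from 0.88, the expected lower limit is below 0.80 at the smallest share tried (0.05%), and kappa itself falls below 0.80 at about 8%, or 6 patients.

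**The case against.** The strongest objection is that the decisive quantity is not in the document. The article does not say how patients aged 65 and over obtain aspirin, or whether the database captures it. If nearly all of it is prescribed and claimed, f is near zero and the problem disappears. That stands: the mechanism follows from the text, but its size does not.

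Nor does the article say where 0.88 comes from. It may already allow for some incompleteness in claims, in which case the right-hand column of the table counts the same loss twice. That also stands, so that column is conditional.

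The problem is partly recoverable. Medication use is collected class by class, and the Limitations section plans a comparison of reported medication use with administrative data that is wider than the composite. Class-level agreement would expose an aspirin gap without new data. This lowers the stakes, but the stated acceptability criterion is still tied to the primary outcome as a whole.

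A reader might infer more than the text supports:

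- **That the criterion is kappa below 0.80.** The 0.80 applies to the lower confidence limit, which is why about 11%, and not 18%, is the relevant figure under otherwise perfect agreement.
- **That a failed validation would overturn the primary result.** The article says only when agreement would be considered acceptable. Nothing makes the primary analysis or the trial's conclusion depend on it.
- **That the medication possession ratio has the same fault.** The article does not say which classes the ratio covers.

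How classes are matched to claims may be detailed in a fuller document. The point does not rest on that omission. It rests on the quantity, reference, criterion and sample size that the article states.

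**Conclusion.** The concern holds in a limited form. As written, the validation compares use of aspirin from any source with prescriptions filled, and aspirin without a claim can by itself lead to failure of the criterion while mimicking over-reporting. With otherwise perfect agreement this happens in expectation at f of about 11%. If 0.88 makes no allowance for unrecorded aspirin, practically any f above 0 is enough, because 138 was sized with no margin.

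The result rests on an assumed f, on p = 0.56 in the validation sample, and on large-sample standard errors. The consequence is a validation result that could not be interpreted. The randomised comparison is unaffected.

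**What to change.** - Apply the lower-limit criterion of 0.80 to the composite of the three prescription classes: statin, beta-blocker, and ACE inhibitor or ARB.
- Recompute the anticipated proportion and the sample size for that composite with the formula in step 1. The three-class proportion cannot be lower than the four-class one. If it lies further above one half than 0.56, p(1−p) shrinks and n rises at the same kappa.
- State what sources of disagreement the anticipated kappa allows for.
- Report agreement class by class. Report aspirin agreement and the four-class composite descriptively, with the caveat that claims may miss aspirin obtained without a prescription. Show the direction of disagreement and not only kappa.
- If a possession ratio is computed for aspirin, give it the same caveat.

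The cost is wording in the analysis plan and possibly a different validation sample size; no new kind of data is needed. The downside is that the criterion no longer covers the primary outcome as defined: its aspirin component stays unvalidated and must be reported as such.
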